## Ethics and Dissemination

### **Ethical Challenges**

The current study is investigating an exposed group, people who have Alzheimer's disease. Even at an early stage in the disease, this group may be considered exposed. For the current study it is important that participants are living at home and the interventions may help them stay home longer. Music and exercise have the health and positive effects on patients with AD, but also generally older people and their caregivers. Nevertheless, there is little high quality research on long-term music and exercise therapy in people with AD. Therefore, this study holds great potential; it is an exploratory study. Little suggests negative effects of song and exercise in people with AD. The literature states that depression and anxiety decreases with music therapy, and well-being increases, but no evidence suggests a stop of disease progression.

The group may not continue to stay home during the intervention, the literature states that depression, anxiety decreases with music therapy, and well-being increases, but it is no evidence that suggests a stop of disease progression. We assume new learning and active use of hippocampus may have positive effects on the brain. If participants move away from home during the period, they will continue to receive the same offers from us. We expect some dropouts from the study, hence we want to test as many patients as possible. If participants no longer wish to do the intervention, but still want to be tested, that will be allowed. If participants wish to do the intervention, but not be tested they will be allowed to do that as well.

fMRI and MR may be experienced as uncomfortable by some participants, but are necessary for the research, however it is not dangerous for the participants.

Retrieval of personal data and neuropsychological tests can also be uncomfortable for some of the participants, but where a computer can be utilized, it will, to limit researcher access and vulnerability of participants.

Music therapy or exercise may not be attractive to everyone. Song has ecological validity in our everyday lives. We humans often meet and sing in different contexts, such as for weddings, funerals, in church, at work and school. We will also ask participants what they prefer of singing,

exercise and no intervention. Although the study will randomise participants, it will indicate why some choose to drop out. The hope is that all participants who are recruited will get enough insight into the study to know that singing lessons, exercise or nothing are the options for participating in the experiment.

The biggest challenge is the control group that will not get any intervention. For the current study, participants are not to be medicated by us, but singing and exercise can be considered a kind of treatment, while the control group is not receiving any treatment. Regular medical treatment that patients usually use is acceptable and they will continue with it during the trial period. That is, the participants get the best beneficial treatment as established in medical research. Music and exercise are two of the best options for non-medical treatment, therefore all groups will receive good treatment. As mentioned in the background section, music and exercise are two of the best options for non-medical treatment, therefore all groups will receive good treatment.

For the current project, co-authorship might become problematic. As there will be three PhD positions on the project, they will all want to be first author on the publications. There are also a limit to how many articles one project can yield. Also as the project has many partners, there might be difficult to detect when which authors should be mentioned in articles or not.

As the project cooperates with Bergen municipality positive findings will be implemented into the health care system. Betterment of health care is a positive implication of the possible findings. However, new music treatment which works may demote other research of being implemented, or research to be done in the field at all. For music may be good medication, it might not be a cure for AD. Also because this is a massive study, which takes time and money, others may not replicate it. Which is why the societal implications of the findings might be negative as well as positive.

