### **Eligibility Criteria**

All adults with AD, above the age of 18, of any gender, are eligible to participate. In addition to having a diagnosis of AD, participants must live at home (not in a residential aged care facility, however they may have plans to move to such a facility in the future) and be able to give informed consent for the study. They also need to be able to complete questionnaires in Norwegian, to undergo magnetic resonance scans, and to attend intervention and assessment sessions in the area of Bergen, Norway. Participants can be non-musicians, amateur/hobby musicians, or professional musicians.

If participants move to a nursing home during the intervention period, they will not be excluded. All participants randomised will be retained and analysed, according to the intention-to-treat principle (see Statistical analyses).

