## **Assessment of Attendance and Fidelity**

Participation in the program will be documented by the therapists in charge of the intervention by simply marking if the participants attend the intervention. 80 % participation is required for inclusion in analysis.

Mid intervention we will also interview participants about how they like their therapist and the therapy, and if they are doing the interventions on their own at home. However, there will be no strict measures of whether they do the intervention on their own. This is encouraged, but not a must.

There will be a midway evaluation of therapists for both the active interventions. Here we will inquire if they overlapped in any way. Both will be asked the same questions:

«Did you use music?», «Did you use exercise?»

Then we will ask the participants the same questions about the therapy sessions. This includes double self-reports from therapists and participants. In addition we will ask participants for their compliance, or how much they practiced on their own.

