## **Statistical Methods**

All primary analysis will be conducted in the modified intention-to-treat population, i.e. all who were randomised and for whom outcome data are available will be analysed in the group to which they were randomised, regardless of whether they received the full intended intervention. All continuous variables will be screened for normality of distributions. If normality is confirmed, the three interventions will be tested in an overall test (one-way ANOVA with three levels), followed by multiplicity-adjusted post-hoc t-tests (as described in Statistical analyses below). However, only one comparison – music intervention versus standard care – is regarded as the primary comparison. Multiplicity adjustment is made for the two primary outcomes, leading to a two-sided 2.5% significance level. All other comparisons and outcomes are regarded as exploratory secondary and are not multiplicity-adjusted (i.e. will be tested on a two-sided 5% level). Additional sensitivity analyses will be conducted on the per-protocol population (by treatment received). Subgroups such as gender, education will also be investigated. Adjusted measures will be music aptitude at baseline. Working alliance will be examined as a mediator variable of later clinical outcomes.

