## Appendix D Testing protocol

### Forskningsprotokoll Tester

*Testing foregår inne på rommet ved siden av fMRI rommet. Hente lånekort i U3 skanneren. Sett deltakeren i den svarte sofaen, og sett deg i den svarte stolen som vende mot sofa.*

“Hei, kjekt at du er med på prosjektet. I dag skal vi gjennom en del tester og spørreskjema og lignende. Først så trenger jeg at du skriver under på denne erklæringen om informert samtykke. Les den først og si ifra hvis det er noe som er uklart.”

*La deltakeren lese gjennom informert samtykkeskjema, dette tar ofte litt tid. Gjør klar alle skjemane dere skal gjennom mens du venter. Signer så samtykke skjema du også, med navn, dato og rolle på prosjektet.*

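### Participants may keep the intervention untested, and those who stop are tested only if they wish, with no reduced assessment, so the 12-month GDS can be lost for people still in contact

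*Protocol*

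**What the plan says.** Ethical Challenges deals with people who want only part of the trial. On those who leave the intervention it says: "If participants no longer wish to do the intervention, but still want to be tested, that will be allowed". On the reverse case it says: "If participants wish to do the intervention, but not be tested they will be allowed to do that as well". The only statement of intent nearby is "We expect some dropouts from the study, hence we want to test as many patients as possible".

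Three sections say who is analysed, and they differ:

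- Eligibility Criteria: "All participants randomised will be retained and analysed, according to the intention-to-treat principle".
- Statistical Methods, defining a modified intention-to-treat population: "all who were randomised and for whom outcome data are available will be analysed in the group to which they were randomised".
- Assessment of Attendance and Fidelity: "80 % participation is required for inclusion in analysis".

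Secondary Behavioural Outcomes places the GDS before randomisation and at 12 months only. The 6-month evaluation under Other Measures covers the therapy and the working alliance, not the GDS. The GDS has 15 yes/no items, is done on paper (Handling and Reporting of Adverse Events), and is filled in by the participant with help if needed (Appendix D, item 4).

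Appendix D gives the only testing procedure and locates it in the room beside the scanner: "Testing foregår inne på rommet ved siden av fMRI rommet". No reduced or off-site version is described.

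**The concern.** Whether a participant is measured at 12 months is trial conduct, and it has to be fixed in the protocol. A statistical analysis plan can say how missing values are handled, but it cannot recover a GDS that was never collected. With one post-baseline value, a single missed assessment leaves no change score, and the person drops out of the primary analysis.

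Much of this loss could be avoided. The singing teacher meets each participant weekly at home or at a day centre, and the exercise group meets weekly. People who move keep their place in the trial, and a form on residence goes out near the end of the project. A short paper scale could be obtained through such contacts from some of those who do not want the full session. At stake are the size of the evaluable sample and, if those who go untested differ from those who are tested, the comparison of music with standard care on a primary outcome.

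**Working it through.** **The passages side by side**

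1. A participant uses the option to have lessons without tests, or stops the lessons and does not ask to be tested. Ethical Challenges permits both.
2. There is then no 12-month GDS, and no earlier post-baseline value to stand in for it (Secondary Behavioural Outcomes).
3. Statistical Methods leaves this person out of the primary analysis because outcome data are missing.
4. Eligibility Criteria says the person is kept and analysed. Steps 3 and 4 cannot both hold.
5. The 80% participation rule adds a third criterion, which fits neither of the other two as a rule for the primary analysis.

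**The plan's own figure**

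Inputs from Sample Size: d = 0.7, two-sided 2.5%, 80% power, 40 per group, 45 recruited per group.

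- Normal approximation: n = 2(z₀.₉₈₇₅ + z₀.₈₀)²/d² = 2(2.241 + 0.842)²/0.49 = 38.8, so 39 per group.
- Noncentral t: n = 40.08 per group, and power at 40 is 79.9%.

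The stated 40 reproduces. The attrition allowance is 5/45 = 11.1% from all causes. No dropout rate is stated.

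**Power if outcome loss differs from the allowance**

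With 45 randomised per group and loss L, n = 45(1 − L) and the noncentrality parameter is 0.7√(n/2). The loss rates of 20% and 30% are assumptions.

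| Loss | n per group | Noncentrality | Power |
|---|---|---|---|
| 0% | 45 | 3.32 | 84.9% |
| 11.1% | 40 | 3.13 | 79.9% |
| 20% | 36 | 2.97 | 75.0% |
| 30% | 31.5 | 2.78 | 68.4% |

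If only the music arm loses more and controls stay at 40, power is 77.4% with 36 music participants and 74.4% with 32. To keep 40 evaluable, recruitment per group would have to be 40/0.80 = 50 at 20% loss, and 40/0.70 = 57.1, so 58, at 30%.

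**Possible bias, by assumption only**

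If a fraction f of an arm is untested, and their mean GDS change differs from that of the tested by D SD, the complete-case mean of that arm is off by f × D. With the same D in both arms, the between-arm difference is off by (f₁ − f₀) × D.

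- Equal loss in both arms: 0.
- 20% against 10%, D = 0.5: 0.10 × 0.5 = 0.05 SD, or 7% of 0.7.
- 30% against 10%, D = 0.5 to 1.0: 0.10 to 0.20 SD, or 14% to 29% of 0.7.

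The sign depends on which arm loses more and on whether the untested fare worse or better. The protocol gives none of these values.

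**The case against.** The strongest reply is that the quoted sentence states a participant's freedom, in an ethics section, and that this freedom must stay. The same paragraph offers testing to people who have stopped, which suits intention-to-treat, and states a wish to test as many as possible. This is right as far as it goes. The gap is that testing after stopping depends on the participant's wish, and that nothing lies between the full session and no data.

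Several stronger readings are tempting, and the documents do not support them:

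- **That missing the scan forfeits the GDS.** No section says so. In Appendix D the GDS is item 4 and the scanner is item 10, and the availability rule in Statistical Methods can be read outcome by outcome.
- **That the 12-month session is the whole of Appendix D.** That text reads as a baseline script, with a welcome and consent. Other Measures schedules the background questionnaire, SPPB and PROMS before randomisation only, so three of the nine items ahead of the scan fall away.
- **That people who move to a nursing home are dropped.** Eligibility Criteria and Ethical Challenges say the opposite, although neither says where they would be tested.
- **That the option biases music against standard care in a known direction.** Only the active arms have an intervention to keep, so the option is asymmetric. That does not show unequal loss: a control who declines also has a missing outcome, and continued lessons might make testing more likely.

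It is also fair that some who decline testing will decline the GDS too, and that the protocol itself limits the scale to mild dementia. A score obtained off-site from someone who has deteriorated may be less valid. Both limit what the change can achieve; neither is a reason not to ask.

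**Conclusion.** The point holds as a gap in trial conduct together with an inconsistency about who is analysed. As written, the protocol permits avoidable loss of a primary outcome in people it still reaches, and it does so against its own promise to keep and analyse everyone. The loss is permitted, not certain.

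Its amount, its direction and any imbalance between arms are unknown. The fall in power to about 75% or 68%, and the shifts of 0.05 to 0.20 SD, are illustrations that rest on assumed loss rates and assumed differences between tested and untested participants. The sample size arithmetic is not at fault. Brain age is exposed to the same option, and a paper fallback cannot rescue it. The change is worth making because it is cheap and cannot be made up for at the analysis stage.

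**What to change.** 1. In Ethical Challenges, keep the right to decline, and state that the 12-month assessment is the default for every randomised participant, whether or not they continue the intervention.
2. For those who decline the full session, offer a reduced set in order: the tests without MRI; failing that, the paper GDS and place of residence, off-site if needed. Record place and mode of completion and whether help was given.
3. Count a participant as lost to follow-up only if they refuse this minimum.
4. Reconcile Eligibility Criteria, the 80% rule in Assessment of Attendance and Fidelity, and Statistical Methods, so that one statement says who enters the primary analysis of each primary outcome.

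The cost is protocol wording and some short GDS collections outside the hospital. The downside is that place and mode will differ for a few participants, probably those of most interest. The recorded details allow the analysis to check whether this matters.

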### **Plan for Publication and Utilisation of Research Results**

Publishing is scheduled in magazines and peer reviewed papers. We also plan a separate website with material and results after they arrive. If the results are positive, we will, in cooperation with the municipality of Bergen, develop a program for better health for Alzheimer's patients. We will help Bergen Municipality and others to train music therapists and give them access to the music and material we have used. Initially all the material will be given free of charge to all municipalities in Hordaland

# Appendix

## Appendix A Singing lessons

Sangundervisning/sangtimer

Tid: 60 min

### Oppvarming – 15 minutter

Tøy og bøy

- a. Strekke armene mot taket, hold pusten, ta armene ned – slipp pusten ut (Høge fjell og djupe daler).
- b. Rulle på skuldrane, begge veier (Anne Malene)
- c. Strekke fingrane / rotere handledda (Mamma, får eg lov å gå på kino)
- d. Strekke beina (Nidelven)
- e. Trampe takt (O Marie, Pengegaloppen, Bedre og bedre dag for dag, Davy Crockett, Napoleon med sin hær)
- f. Hæl / tå (Mellom bakker og berg 1.vers)
- g. Ro- øvelser (En sjømann elsker havets våg)

Mia o Maria Mia o Maria

Vioala viola viola viola vi

Ja det var bra ja, bra ja, ja det var bra

### Lekesynging – 20 minutter

Bro bro brille  
Alle fugler små de er  
Jeg gikk en tur på stien  
Pål sine høner  
Ro ro ro din båt  
Fader jacob på flere språk

### Korsang: - 25 min

Månedens sang

Lytting: 5 min

Sangliste

## Appendix B Exercise Lessons

## **Treningsprogram**

Basert på trygg på to bein

Tid: 60 min

### **Oppvarming:**

Velkommen, opprop

#### **Sitte på stol oppvarming:**

Armer – strekk mot taket

Skuldre – Hev, senke, rulle

#### **Stå bak stolen:**

Sving og sikt, skitak ”Ski-tak”, Sving side til side, Sving side – heilt rundt

Gå på staden, Med armsving

Side steg, Ett steg sideveis, fram og tilbake.

#### **Gange bak stolradene:**

Gå framover

Gå bakover – bytt vei

Gå sidesteg – bytt vei

### **Hoveddel:**

#### **Styrkeøvelser:**

Stå bak stolen:

Opp på tå 10x3 repetisjoner

Opp på hæl 10x3 rep

Abduksjon i hofter

Opp på tå, ta side steg 10x3 rep.

Instruer kvar enkelt i å stå stabilt på en fot, evt. start med tyngdeoverføring - 10x3 rep

Knebøy - 10x3 rep

Stå med siden intill stolen:

Knebøy med framfall 10x3, skift bein

Høge kneløft 10x3, skift bein

Knebøy på en fot - 10x3 rep, - skift bein - Støtte på stol. Skift bein 10x3

Sitte på stolen:

Reise seg opp- sitt ned – uten støtte på stol 10 x 3

Reise seg opp- sitt halvveis ned – reis opp – start m 5, så 7 også 10 (3 rep)

Reise seg opp- sitt halvveis ned og hald stillingen i 3 sekund- reis opp - Støtte på låra i starten, gradvis uten støtte og lenger hald.

Reise seg opp- sitt nesten ned- raskt opp igjen - ”Tegnestift på stolen” 10 rep, auke til 10x3

Reise seg opp på matte, leg matte intil stolen.

Gå med høye kneløft rundt i rommet

#### **Balanseøvelser:**

sitte på stolen – reise seg, gå rundt stolen rolig.

Reise opp, sidesteg til neste stol, sitt ned. - gjenta rundt hele sirkel

Reise opp og sitt ned og bytt beina.

Stå bak stolen:

Stå med samla bein, Med åpne øyne

Stå med samla bein - Med lukkede øyne- tell til 5 i starten.

Stå i gangstilling -Med sida mot stolen. Tyngdeoverføring fram/tilbake

Stå på en fot -Støtte på stol i starten. Skifte bein.

Snu rundt 360 grader, rolig og skift retning

To sidesteg til høyre - opp på tå - to sidesteg til venstre

Slalåm mellom stolene – gå en runde

Gå rolig. Skift retning - Gjenta 5 ganger

Gå med vekselvis -”musesteg” og lange steg framover

Gå og bære - glas/pappkrus med vatn

Gå over stepkasse - Støtte ved behov.

Gå på airex matte med små erteposer el skjult under.

Ballkast ved gange Personstøtte ved behov - Støtte ved behov

Terapeut kaster ball til gående deltakere – tilfeldig rekkefølge.

Stå ved vegg eller ribbevegg - Steppe Frontsteg, sidesteg, steg over step

I gangbane Stående med stol framfor

Stående med stol bak

Stående med sida inntil stol

Inntil vegg - Gå på strek

Stå på en fot - Tape strek eller legg treningsstrikk på golvet, gå framover, bakover, sideveis reduser støtte etter kvart. Skift bein

Ballkast med terapeut - Varier med sidesteg mellom kvart mottak.

Stå i tandemstilling Gå på matte(r) Begynn gjerne i gangstilling og reduser understøttelsesflate etterkvart

Gå i ulike retninger, evt. sikre med stoler

Inntil vegg eller mellom to stoler

Sitte på stol Stå på matte(r) Gangstilling, beina sammen, tandemstilling.

Oppreising Ulike varianter av oppreising som over.

Leker som mus og katt osv.

### **Nedvarming:**

Tøye ut, nedvarming – gjør det som passer for gruppa, sitt på stol. Slappe av, puste ut.

## Appendix C Music used for the brain scans

Music for the scanner, deltakerne får velge en av følgende sjangere:

1. Klassisk stykke - Praetorius Six Dances from Terpsichore

<https://www.youtube.com/watch?v=kmHR6GWQOWU>

2. Rock – Wild Melodic Metal | Guitar Backing Track Jam

<https://www.youtube.com/watch?v=R0jwsidG4wU>

3. World - PAN FLUTE PERU - INKA TRAIL - CAMINO INCA

<https://www.youtube.com/watch?v=48FZKfcRauM>

4. Jazz –Modern jazz gypsy

<https://www.youtube.com/watch?v=YkrxvqGbqgk>

5. Pop – 80s Pop Funk Backing Track (Dm) | 110 bpm - MegaBackingTracks

<https://www.youtube.com/watch?v=tD8AtHHvzJs>

6. Folk - samme som World

NB: Alle sangene har blitt behandlet i Audacity og endret til 74 decibel (dB) og normalisert for lydvariation. Alle sangene er også blitt kuttet og satt sammen til å vare 8 minutter. Selve skanningen varer 7.14 minutter.

## Appendix D Testing protocol

### Forskningsprotokoll Tester

*Testing foregår inne på rommet ved siden av fMRI rommet. Hente lånekort i U3 skanneren. Sett deltakeren i den svarte sofaen, og sett deg i den svarte stolen som vende mot sofa.*

“Hei, kjekt at du er med på prosjektet. I dag skal vi gjennom en del tester og spørreskjema og lignende. Først så trenger jeg at du skriver under på denne erklæringen om informert samtykke. Les den først og si ifra hvis det er noe som er uklart.”

*La deltakeren lese gjennom informert samtykkeskjema, dette tar ofte litt tid. Gjør klar alle skjemane dere skal gjennom mens du venter. Signer så samtykke skjema du også, med navn, dato og rolle på prosjektet.*

#### 1. Spørreskjema

“Jeg vil du skal fylle ut dette skjema, bare spør hvis det er noe som er utydelig,”

*Gi deltakeren blyant så de kan fylle ut, ikke overvåk dem. Hvis det er åpenbart at de står fast, hjelp.*

#### 2. Ord læringsliste

“Flott, du gjør det kjempe bra. Nå skal vi se på litt ordlæring og husking av en ordliste. Først får du en ordliste med ti hverdagslige ord, jeg viser deg arket også vill jeg at du skal lese høyt hva som står der, etterpå vil jeg at du skal si alle ordene du nettop leste.”

*Vis deltakeren ordene i riktig rekkefølge med to sekunders intervall, rekkefølge 1. Hvis deltaker ikke kan lese et ord, les det til ham og skriv det ned for det tilsvarende ordet i kolonnen «Kan ikke lese».*

